## Background

### Rationale

Vascular access via central venous catheters (CVCs) is essential for acute patient care in the Intensive Care Unit (ICU) [1]. Despite the utility of CVCs, they have been identified as a risk factor for bloodstream infection that, when not recognized early, can progress to sepsis [2, 3]. CVCs are the most common cause of nosocomial bloodstream infection [4]. A report by the National Nosocomial Infections Surveillance System identified that 87% of all primary bloodstream infections occur in patients with a CVC [5]. Additionally, the relative risk for bloodstream infection is 64 times greater for patients with a CVC compared to patients with only peripheral venous catheters [4]. Instances of bloodstream infection in patients with a CVC are formally referred to as central line-associated bloodstream infection (CLABSI) [1, 6]. Critically ill patients are among those most likely to develop CLABSI [7, 8] with incidence as high as 6.9 per 1000 catheter days [9–12]. Evidence suggests that CLABSI impacts patient mortality and increases in-hospital length-of-stay (LOS) readmissions and costs. A systematic review of 18 studies by Ziegler and colleagues found that CLABSI has a substantial attributable mortality, with an odds ratio of 2.75 for in-hospital death [13]. A 2013 meta-analysis of the burden of hospital-acquired infections (HAIs) in the USA found CLABSI has one of the highest attributable LOS of any HAI at 15.7 days, second only to *Methicillin-resistant Staphylococcus aureus* surgical site infection [14]. A retrospective case-controlled cohort study of 11,802 hospitalizations in the USA reported that 10.4% more CLABSI patients were readmitted to a hospital within 30 days of discharge compared to non-CLABSI patients [15]. CLABSI also presents a significant economic burden, increasing healthcare costs by an average of USD 45,814 per case [14, 16, 17].

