ARROW SS-14703	ARROW multi-lumen central venous catheter	Triple lumen (per lumen)	10.0	0.5
ARROW SI-09880	ARROW percutaneous sheath introducer set	Cordis (side-arm lumen of introducer)	10.0	2.5
PICC lines	PICC lines	PICC line (per lumen)	20.0	0.5
ARROW CA-22122-F	ARROW temporary two-lumen hemodialysis catheter	Temporary hemodialysis catheter 12Fr (per lumen)	10.0	2.5^a^
MAHURKAR Elite 8888212216	Covidien MAHURKAR elite acute hemodialysis dual lumen catheter kit 13.5Fr	Acute dual lumen hemodialysis catheter 13.5Fr (per lumen)	10.0	2.5^a^

^a^4% sodium citrate solution

**Additional file 4** Instructional video on procedures for participants allocated to CHG locking device.

A single set of blood cultures will be drawn from the CVC of all study participants every 48 h beginning on the day of study enrolment until the patient has all CVCs removed, has a documented infection, or leaves the ICU. Blood cultures will be analyzed for infectious organisms in the core laboratory of the HGH.

The bedside nursing staff will perform the assigned interventions. Bedside nurses will document flushing and instillation of CHG on study-specific logs, which will be checked daily by the research staff. The only exception to the above procedures is flushing and locking of temporary and acute dialysis catheters will be carried out using 4% Sodium Citrate solution rather than 0.9% NS.

We will approach principal investigators (PIs) and research coordinators of all other studies conducted in the ICU to determine co-enrolment eligibility.

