## Outcomes

The primary outcomes of the ChloraLock^TM^ pilot trial relate to the feasibility of conducting a larger RCT.
*Consent rate* will be measured as the proportion of patients and SDMs approached who consent to participate in the trial; a successful consent rate will be defined as ≥ 80%. Consent rates will be reviewed on a monthly basis to improve enrolment practices.*Recruitment rate* will be measured as the proportion of patients eligible to participate who are randomized to the trial; successful accrual will be defined as ≥ 80%; we anticipate achieving enrolment of 100 patients within 50 weeks with an average of 2 patients enrolled per week. Screening logs will be reviewed on a weekly basis to determine eligibility rates.*Protocol adherence* will be measured as the proportion of instances when ChloraLock^TM^ is used during flushing and locking procedures; since this will be difficult to capture in a busy ICU setting, flushing and locking logs will be used as a surrogate to capture adherence. Successful protocol adherence will be ≥ 90% compliance with device use.*Level of comfort with the trial protocol* staff comfort with ChloraLock^TM^ and the trial protocol will be measured using repeated surveys throughout the duration of the trial. Vetted suggestions will be incorporated into the protocol.

The ChloraLock^TM^ pilot trial also includes secondary, clinical outcomes related to the antimicrobial efficacy of the device and prevention of central line infections.
*Central line colonization*: Rates of central line colonization in each study arm will be documented. We will define central line colonization as a positive central line culture with concurrent negative peripheral stab culture. We will not order peripheral stab cultures to avoid harm, but will collect data from those ordered by the treating team.*Bacteremia*: Rates of bacteremia in each study arm will be documented. We will define bacteremia as a positive peripheral stab culture and correlations will be done with central line cultures.*Clinical end points* will be documented for each study arm:
LOS in ICULOS in hospitalICU mortality at 28 daysHospital mortality at 28 days

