### Statistical analysis

Simple descriptive statistics will be used for feasibility outcomes and baseline demographics (Table 3). Continuous data will be tested for normality using histograms, Normal Q-Q plots, skewness, kurtosis, and the Shapiro–Wilk test. Normally distributed data will be summarized using mean and standard deviation, non-normal data will be summarized using median and interquartile range, and categorical variables will be summarized using number and percent proportion. The two treatment arms will be compared by simple statistics as the study may not be powered for the secondary outcomes. However, we will test group differences with either the independent-samples t-test or the Mann–Whitney U test. Somers’ delta (*d*) will be used to identify and measure the strength and direction of association that exists between two ordinal variables, particularly for the number of positive cultures. If there is a large treatment effect between groups, this may aid the sponsor in proceeding with larger RCT as required for regulatory approval within other countries. All statistical tests will be conducted using SPSS version 24 (IBM Corp, Armonk, NY).

**Table 3 Tab3:** Summary of primary and secondary outcomes for the ChloraLock^TM^ pilot trial

Pilot trial outcomes	Analysis	Pass threshold
Primary outcomes		
1. Consent rate: patients and SDMs approached who consent to randomization	Proportion	≥ 80%
2. Recruitment rate: eligible patients who are randomized	Proportion	≥ 80%
3. Protocol adherence: times ChloraLock^TM^ is used in conjunction with usual locking procedures	Proportion	≥ 90%
4. Comfort: staff comfort level with the device and trial protocol	Descriptive	NA
Secondary outcomes		
1. Central line colonization: assessed for each arm as positive central line culture and negative peripheral poke	Proportion	NA
2. Bacteremia: assessed for each arm as positive stab cultures	Proportion	NA
3. Clinical end points: LOS in ICU, LOS in hospital, ICU mortality at 28 days, hospital mortality at 28 days	Median or mean proportions	NA

Given the small sample size and the focus on feasibility outcomes, there will be no subgroup analyses or interim analyses. We will adhere to the intention to treat principle.

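### The culture outcomes set no organism or confirmation rule, so a contaminated peripheral stab counts as bacteremia and a contaminated line draw with a paired negative stab counts as colonization

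*Protocol article*

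**What the plan says.** The Outcomes section of the protocol article defines two secondary microbiological outcomes.

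- Colonization: "We will define central line colonization as a positive central line culture with concurrent negative peripheral stab culture".
- Bacteremia: "We will define bacteremia as a positive peripheral stab culture and correlations will be done with central line cultures".

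Table 3, under Statistical analysis, repeats both. Colonization is "assessed for each arm as positive central line culture and negative peripheral poke", and the other row reads "Bacteremia: assessed for each arm as positive stab cultures". Each is analysed as a proportion, with no pass threshold.

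On sampling, which starts at enrolment, the Interventions section says: "A single set of blood cultures will be drawn from the CVC of all study participants every 48 h beginning on the day of study". On the peripheral culture, Outcomes says: "We will not order peripheral stab cultures to avoid harm, but will collect data from those ordered by the treating team".

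The only text about organisms is in Interventions: "Blood cultures will be analyzed for infectious organisms in the core laboratory of the HGH". It gives no list and no rule for contaminants.

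Statistical analysis also plans Somers' d, in particular for how many cultures are positive. It attaches no pairing or contaminant condition to that count.

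**The concern.** Both definitions are operational: a data abstractor could apply them as written. Applied that way, they do not separate a skin organism picked up at the draw from an organism living in the line or the blood.

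- **Bacteremia.** One peripheral stab growing a skin commensal is an event, even if the concurrent line culture is negative. It carries the same weight as a recognised pathogen grown from both sites.
- **Colonization.** A contaminated line draw with a sterile peripheral culture gives exactly the line-positive, periphery-negative pattern that defines the outcome. The negative stab removes bacteremia but does not remove line-draw contaminants.
- **Number of positive cultures.** The trial itself schedules only CVC cultures. On the plain reading, every contaminated 48-hour draw adds to this count, paired or not.

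These outcomes carry the trial's preliminary efficacy objective, and Statistical analysis says a large treatment effect may help the sponsor decide to proceed. Evaluators are not blinded (Study design). Without a rule set beforehand, any later decision to set aside a positive as contamination would be made knowing the arm.

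**Working it through.** The protocol states no event rate, contamination rate or power for the culture outcomes, so there is no figure of its own to reproduce. The check has two parts.

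**1. Literal scoring of the definitions**

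| Line culture | Concurrent peripheral stab | Colonization | Bacteremia | Count of positives |
|---|---|---|---|---|
| Contaminant | None ordered | No | No | Yes |
| Contaminant | Negative | Yes | No | Yes |
| Negative | Contaminant | No | Yes | Yes, if stabs are counted |
| Pathogen | Same pathogen | No | Yes | Yes |

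The planned correlation of stab results with line cultures does not change any cell. Neither does the statement about what the core laboratory looks for.

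**2. Illustration of size**

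All inputs are assumptions except the 50 per arm and the 48-hour interval.

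- Catheter time of 7 days, so draws on days 0, 2, 4 and 6: k = 4 per patient, 400 for 100 patients.
- Contamination per draw c = 1%, 2% or 3%.
- Pairing share q: the share of positive line draws that have a concurrent negative stab.

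Patients per 100 with at least one scorable contaminated draw = 100 × [1 − (1 − cq)^4]:

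| | c = 1% | c = 2% | c = 3% |
|---|---|---|---|
| q = 1 (also the unpaired culture count) | 3.9 | 7.8 | 11.5 |
| q = 0.5 | 2.0 | 3.9 | 5.9 |
| q = 0.25 | 1.0 | 2.0 | 3.0 |
| q = 0.1 | 0.4 | 0.8 | 1.2 |

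The first row applies to the number-of-positive-cultures analysis, put as patients with at least one contaminated draw. The lower rows apply to colonization as defined.

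*Dilution.* Assume true risks of 10% and 5% (risk ratio 0.50) and the same contaminant risk f in both arms. The observed risk is 1 − (1 − t)(1 − f). With q = 1:

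- c = 1%, f = 3.9%: 13.5% vs 8.7%, ratio 0.65.
- c = 2%, f = 7.8%: 17.0% vs 12.4%, ratio 0.73.
- c = 3%, f = 11.5%: 20.3% vs 15.9%, ratio 0.78.

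True colonization also needs the paired negative stab to be counted. If pairing is unrelated to cause (an assumption), q shrinks both parts. At c = 2% and q = 0.25, true risks become 2.5% and 1.25% and f becomes 2.0%. The observed risks are 4.4% and 3.2%, ratio 0.72. Sparse pairing lowers the counts but hardly changes the dilution.

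Power at 50 per arm (two-sided 5%, normal approximation for two proportions) for 10% vs 5% is about 16%. With f = 8% the risks are 17.2% vs 12.6%, and power is about 9%. It is low either way.

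*Effect of asking for a second positive.* With 4 draws and q = 1, the probability of two or more contaminated draws is 1 − (1 − c)^4 − 4c(1 − c)^3. Per 100 patients this is 0.06, 0.23 and 0.52 at c = 1%, 2% and 3%, against 3.9, 7.8 and 11.5 for any positive.

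**The case against.** Several objections have force.

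- **A scheduled CVC draw alone is neither event.** A reader might infer that any single positive line culture scores as colonization or bacteremia. The definitions do not support that. Colonization also needs a concurrent negative stab, which the trial does not order, and bacteremia needs a positive stab. The 48-hour schedule therefore does not multiply false bacteremia, and it multiplies false colonization only through clinician-ordered pairs. This stands. It does not touch the number-of-positive-cultures analysis, which has no pairing condition.
- **Contaminants need not outnumber true events.** A reader might infer that they do by setting them against the Rationale's CLABSI figure, "with incidence as high as 6.9 per 1000 catheter days". That is a stated maximum for bloodstream infection, not a colonization rate, and a bloodstream infection with a positive stab is excluded from colonization by definition. No true colonization rate is given, so the comparison cannot be made.
- **The direction depends on equal contamination.** The device puts a biocide into the lumen from which the culture is drawn, so equal contaminant yield by arm is an assumption.
- **Skin flora can be genuine colonizers.** Making a repeat positive 48 hours later the main colonization definition could favour the device, because it might clear an organism before the second draw in one arm only. This stands and shapes the fix.
- **The outcomes are secondary, without pass thresholds, in a pilot that says it may not be powered for them.** This limits the consequence.
- **A condensed article may leave organism coding to a fuller document.** That excuses omitted detail. Here, though, the article states both definitions in full, twice, and as stated they count contaminants.

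**Conclusion.** The point holds in limited form. As written, the definitions count one contaminated peripheral stab as bacteremia and a contaminated line draw with a paired negative stab as colonization. The planned count of positive cultures has no contaminant rule at all.

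If contamination is similar in the two arms, non-infection events are added to both and the preliminary efficacy comparison moves towards no difference. The risk ratios of 0.65 to 0.78 in place of 0.50 show how this works under assumed inputs. They are not estimates for this trial, because the article gives no contamination rate, pairing rate, catheter duration or true colonization rate.

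A reader might also infer that an inflated event rate will be carried into the sample size of the larger trial. The article does not say so: its Discussion speaks of recruitment, consent and adherence informing the next trial, and Statistical analysis says only that a large effect may aid the sponsor.

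The change is worth making because it is cheap and because a rule fixed before analysis keeps unblinded judgement out of the classification. The primary feasibility outcomes are not affected.

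**What to change.** **Bacteremia (Outcomes and Table 3).** Count a recognised pathogen in one peripheral culture. Count a common skin commensal only when the same organism grows in a second, separate culture, which may be another peripheral set or the concurrent CVC set. Keep the any-positive count as a sensitivity analysis.

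**Colonization and the number of positive cultures.** Keep the stated definition and count. By a rule written before analysis, report three groups separately by arm: pathogens, repeat-positive commensals and single unconfirmed commensals. Use the repeat-positive version as a sensitivity analysis only, for the reason given above about clearance by the biocide.

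**Cost.** Two definitions are reworded, a short organism list is written, and organism names the laboratory already reports are recorded. No extra cultures are drawn. Fewer bacteremia events will be counted. Some commensals found at the last draw will stay unconfirmed, since culturing ends when all CVCs are out, an infection is documented or the patient leaves the ICU. The any-positive count shows how much this matters.

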## Methods

### Study design

The ChloraLock^TM^ pilot trial is a single centre, open-label, two-arm, parallel-group feasibility RCT. Randomization will be performed with a 1:1 allocation, and study participants and evaluators will not be blinded to intervention assignment due to lack of placebo ChloraLock^TM^ devices. Order of randomization will be concealed by means of random number generator and sealed envelopes (see Allocation and Blinding details below). Patients will be recruited from the ICU at the Hamilton General Hospital (HGH) within 72 h of admission if they have a CVC in situ. The primary objectives of the ChloraLock^TM^ pilot trial are to assess uptake of the trial protocol and ChloraLock^TM^ device by ICU staff and determine the feasibility of conducting a large RCT to investigate our overall research question. Secondary objectives are related to the clinical efficacy of the ChloraLock^TM^ device. ICU nurses will be responsible for using the ChloraLock^TM^ device and operationalizing the protocol; therefore, we will be collecting data on their perceptions of the trial using a voluntary survey. Feasibility and survey data will be used to inform the conduct of a larger RCT.

This protocol adheres to the Standard Protocol Items: Recommendations for International Trials (SPIRIT) guidelines and is formatted in accordance with the SPIRIT 2013 checklist (see Additional file 1) with all required items [34, 35]. The World Health Organization Trial Registration Dataset (see Additional file 2) and a schedule of enrollment, interventions, and assessments (Table 1) are included. Prior to enrolment of our first participant, the protocol was registered at ClinicalTrials.gov (NCT03309137).

**Table 1 Tab1:** SPIRIT figure detailing enrolment, interventions, and assessment

Timepoint	Study period							
	Enrolment	Allocation	Post-allocation					Close-out
	< 72 h post ICU admission (*-t*_1_)	0	t_1_	t_2_	t_3_	*t*_4_	etc.	intervention discontinued (*t*_*x*_)
Enrolment								
Eligibility screen	X							
Informed consent	X							
Allocation		X						
Interventions								
Usual care		X	X	X	X	X	X	
CHG locking device		X	X	X	X	X	X	
Assessments								
Baseline variables	X	X						
Recruitment rate	X	X						
Consent rate	X	X						
Initiation of study procedures		X						
Protocol adherence			X	X	X	X	X	
Comfort level			X	X	X	X	X	
Central line colonization			X	X	X	X	X	
Bacteremia			X	X	X	X	X	
LOS in ICU								X
LOS in hospital								X
ICU mortality at 28 days								X

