### Interventions

Patients will be randomized in a 1:1 ratio to either (1) usual care, or (2) CHG locking device.

Standard flushing and locking practices of central and peripheral venous catheters will be continued for participants allocated to ‘usual care’. All venous catheters will be flushed with a pre-specified volume of 0.9% Normal Saline (NS) solution ranging from 3 to 30 mL. As per hospital approved protocol, venous catheters will be flushed in a turbulent fashion to promote patency of the internal lumen. Catheters that are not infusing will be capped with a Luer lock adapter and considered locked. An additional movie file shows procedures for participants allocated to usual care in more detail (see Additional file 3).

**Additional file 3** Instructional video on procedures for participants allocated to usual care.

Participants allocated to ‘CHG locking device’ will receive ChloraLock^TM^ instillation addition to usual care. Venous catheters that are not infusing will be flushed with 0.9% NS solution as per hospital-approved protocol. Subsequently, ChloraLock^TM^ will be Luer locked onto a 3-mL 0.9% NS prefilled Posiflush^TM^ syringe, which will be treated as a single-use device to instill a pre-specified volume of CHG locking solution into the lumen of the venous catheter (Table 2). The catheter will then be capped with a Luer lock adapter and considered locked, thereby containing the CHG locking solution within the lumen. For participants in the CHG locking device group, each venous catheter will be labelled with the pre-specified volume of CHG locking solution required to lock the catheter. Before re-accessing the catheter for further sampling or infusions, all fluid will be aspirated to clear the lumen of CHG. An additional movie file shows procedures for participants allocated to CHG locking device in more detail (see Additional file 4).

**Table 2 Tab2:** Pre-specified flushing and locking volumes

Reference number	Full name	Common name	Flushing volume (mL)	Locking volume (mL)
MED-RX 10-1026	Minibore tubing with slide clamp, thinner lumen extension for peripheral IV	Normal saline lock extension (small bore)	3.0	0.5
MED-RX 10-114RL	Standard bore tubing with slide clamp, thicker lumen extension for peripheral IV	Normal saline lock extension (large bore)	3.0	1.0
Baxter JC 1946	Y-type extension set (1.8cc in total, 1.2cc per line)	Y-normal saline lock extension (per lumen)	3.0	1.0

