### Participant timeline

Participants will be enrolled in the trial from the time of randomization until they leave the ICU. As shown in Fig. 2, data will be collected for the duration of participant ICU admission. For all participants, blood cultures will be drawn at baseline and every 48 h until all CVCs have been discontinued. For patients allocated to CHG locking device, device use will be discontinued when the patient leaves the ICU or all venous catheters have been discontinued.

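### Colonization and bacteremia can be classified only where an unblinded treating team chose to order a peripheral culture, so unequal ordering could create or hide a difference in these secondary outcomes

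*Protocol article*

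**What the plan says.** All references are to the protocol article.

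- **Colonization** (Outcomes): "We will define central line colonization as a positive central line culture with concurrent negative peripheral stab culture".
- **Bacteremia** (Outcomes): "We will define bacteremia as a positive peripheral stab culture and correlations will be done with central line cultures".
- **Where peripheral cultures come from** (Outcomes): "We will not order peripheral stab cultures to avoid harm, but will collect data from those ordered by the treating team".
- **What is scheduled** (Interventions): "A single set of blood cultures will be drawn from the CVC of all study participants every 48 h". The Participant timeline section adds a culture at baseline.
- **Blinding** (Study design): "study participants and evaluators will not be blinded to intervention assignment". The Allocation and blinding section says that physicians and bedside nurses cannot be blinded. The section on adherence strategies describes a sticker on the chart and Kardex that shows the assigned intervention.
- **Analysis** (Statistical analysis): Table 3 repeats both definitions as a proportion per arm, with no pass threshold. The text plans tests of group differences and mentions Somers' d for the number of positive cultures. It adds that a large treatment effect could help the sponsor move to a larger trial.

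**The concern.** Colonization requires a negative peripheral result and bacteremia a positive one. The trial schedules neither. The only culture taken from everyone on a common schedule is the line culture, and that alone cannot assign a patient to either outcome. A positive line culture without a concurrent peripheral culture has no category in the Outcomes section or in Table 3.

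Whether the peripheral culture exists is decided after allocation by clinicians who know the arm. If they order more often in one arm, for example because they trust the device or are wary of it, the proportion classified differs between arms for reasons unrelated to infection. This is verification bias, and it can act in either direction. Analysis cannot repair it, because a culture that was never drawn cannot be recovered.

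Preliminary efficacy is the stated secondary objective, so a misleading contrast could colour the case for a larger trial. The same definitions could also be carried into that trial.

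**Working it through.** The plan states no figure on this point, so there is none to reproduce. The check has two parts: the logic of the definitions, and an illustration of size.

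**1. Which patients can be classified**

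| Line culture | Concurrent peripheral culture | Outcome under the plan |
|---|---|---|
| positive | negative | colonization |
| positive | positive | bacteremia |
| negative | positive | bacteremia |
| positive | not ordered | neither; no category given |

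The last row follows from the definitions alone and needs no assumption about rates.

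**2. Apparent effect when ordering differs**

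From the plan: 50 participants per arm (Sample size).
Assumed: 15% line-culture positive in both arms; a concurrent peripheral culture for 60% of usual-care positives and 30% of CHG positives; the same share of those cultures negative in each arm.

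Classified = n × P(line positive) × P(peripheral ordered | line positive)

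- Line positives per arm: 50 × 0.15 = 7.5
- Usual care: 7.5 × 0.60 = 4.5
- CHG: 7.5 × 0.30 = 2.25
- Apparent risk ratio: 2.25 / 4.5 = 0.5, with no true effect
- Unclassified: (15 − 6.75) / 15 = 55% of positives overall

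The ratio equals the ratio of the ordering proportions and does not depend on the 15%.

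**3. Equal ordering in both arms**

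Unclassified share = 1 − ordering proportion. Ordering of 80%, 50% and 30% leaves 20%, 50% and 70% of positives unclassified. Most are unclassified only if ordering is below 50%.

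**4. The bias can also hide an effect**

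Take true rates of 20% (usual care) and 10% (CHG), with ordering of 30% and 60% respectively: 0.20 × 0.30 = 6% and 0.10 × 0.60 = 6%. A true halving disappears.

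**5. How often this would give a nominally significant result**

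Two-sided Fisher test at 0.05, exact enumeration, 50 per arm, no true effect:

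| True rate, both arms | Peripheral culture always available | Ordering 30% vs 60% |
|---|---|---|
| 10% | 1.8% | 2.0% |
| 15% | 2.4% | 5.2% |
| 20% | 2.8% | 8.6% |
| 30% | 3.1% | 16.5% |

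At rates of 15% or below, the harm is mainly a biased estimate. False significance rises clearly above 5% only at the higher rates. Fisher is used here as a convenient yardstick for two proportions; the plan does not name it.

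**The case against.** **These are secondary outcomes of a feasibility pilot.** Consent, recruitment, adherence and staff comfort are primary, and none depends on a culture. Table 3 sets no pass threshold for the culture outcomes, and the Statistical analysis section concedes that power may be lacking. Not ordering peripheral cultures is a disclosed choice to avoid harm. All of this stands. It lowers the severity but does not cure the definitions.

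**The rates are assumed.** The documents give no ordering rate and no reason to expect a two-fold gap in either direction. In the 15% scenario the Fisher test rejects 5.2% of the time, about nominal, and observed counts of 5 against 2 give p = 0.44. This also stands: the figures show what could happen, not what is expected.

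**The line cultures are not ignored.** The mention of Somers' d for the number of positive cultures suggests some analysis of cultures that need no peripheral result. That is fair, but line-culture positivity is still not a named outcome, and the named ones depend on ordering. A reader might also infer that no preliminary efficacy can be read from the trial at all. That goes too far, since length of stay and mortality need no culture.

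**Baseline positives.** A reader might infer that infections present at enrolment are counted as events. Table 1 marks both outcomes only from the first post-allocation timepoint, and randomisation balances prevalent positives in expectation. What remains is that the definition does not say how a patient already positive at baseline is reported.

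**Aspiration before sampling.** For the CHG arm the Interventions section says: "Before re-accessing the catheter for further sampling or infusions, all fluid will be aspirated to clear the lumen of CHG". A reader might infer that the cultured fluid differs by arm. The documents do not show this. The stated purpose is to remove CHG, which usual care does not contain. The article does not describe how usual-care samples are drawn, and it refers to an additional file, not available here, for usual-care procedures. Silence in a condensed article is not evidence of a difference.

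**Conclusion.** The concern holds for the two culture-based secondary outcomes. As defined, both depend on a test that the trial does not schedule and that unblinded clinicians may or may not order, and a line-positive patient without that test fits neither outcome. This rests on the protocol's text alone.

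The size is unknown. A two-fold difference in ordering would by itself give an apparent risk ratio of 0.5, or could mask a true halving, but the ordering proportions are assumptions. A reader might conclude that most line-positive patients will go unclassified. The documents do not support that as a prediction, because it is true only if ordering falls below 50%.

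The primary feasibility outcomes are untouched. This should be fixed, since the correction is cheap and the definitions could pass into a larger trial, but it does not undermine the pilot's main purpose.

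**What to change.** Change the outcome wording in the Outcomes section and in Table 3:

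1. Name as the main culture-based secondary outcome: at least one positive scheduled central line culture after the baseline culture, in all randomised participants, by arm. Report positives on the baseline culture separately, as prevalent.
2. Keep the peripheral-culture definitions as a descriptive split of line-culture positives into colonization, bacteremia and undetermined (no concurrent peripheral culture).
3. Report by arm how often a concurrent peripheral culture existed among line-culture positives, so that readers can judge whether ordering differed.

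The cost is wording and one extra tabulation. No new culture is needed, because the line culture is already scheduled every 48 h in both arms, and the choice not to order peripheral cultures is kept. The downside is specificity: positivity on the line culture alone includes contaminants, so it measures infection less cleanly than a paired result would.
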